### Recruitment

Patients are accessible for inclusion if they have been treated with radiotherapy for a head and neck cancer in Denmark. Patients will be recruited from the Department of Otorhinolaryngology, Head and Neck Surgery & Audiology, Rigshospitalet, by referral from other departments, e.g. Oncology Departments in Denmark, or can be self-referred, e.g. triggered by media awareness. 

## Methods: assignment of interventions

### Allocation

A predefined randomisation code is established for all 120 patients according to patient treatment order (1–120) from the start of the trial. The randomisation is done randomly in a 1:1 ratio. The allocation sequence is generated using www.randomization.com. Randomisation is performed in blocks of six, three patients receiving ASCs and three patients receiving placebo to avoid clustering of treatments. Within blocks of six, a balanced use of donors will be applied. The randomisation is done by one person, the allocation manager, at the Cardiology Stem Cell Centre, CSCC, The Heart Centre, Rigshospitalet, and the staff involved in the trial is independent of the randomisation. The allocation manager will store the randomisation table, and the table with randomisation numbers will only be available to one specified person at the CSCC, The Heart Centre, Rigshospitalet, until the end of the trial. This person will not be involved in analysing data related to the study endpoints.

For the purpose of safety and potential unblinding, two sets of sealed envelopes containing the randomisation code for each patient are made. One envelope is locked up at the clinical site at the sponsor and is thereby available for the investigator, and one envelope is locked up at the CSCC production facility. The allocation envelopes will be monitored by the GCP unit during the trials to ensure that they are not opened before the end of the study.

### Blinding

This is a double-blinded study. Both the sponsor, investigators, and study staff (except for staff involved in stem cell preparation and staff involved in bioanalytical analyses) and patients will be blinded to treatment assignment. Data analysts will further use a dataset where the groups are masked. The injection syringes of either ASC or placebo will be identical to ensure blinding.

Emergency unblinding can be performed at any time if it is considered necessary by the principal investigator or the sponsor. Participants are issued with “In case of emergency” cards to be carried at all times during the study including an emergency phone number. If the trial or a single subject is prematurely unblinded the principal investigator will document the reason for unblinding and notify the Danish Medical Agency and the National Ethics Committee.

## Methods: data collection, management, and analysis

### Data collection methods

Data is collected at baseline and at follow-up visits at 4 months (+/− 14 days) and after 12 months (+/− 4 weeks) by the principal investigator or a sub-investigator (doctor). Data are recorded on case report forms (CRFs). Unstimulated whole salivary flow rate and stimulated whole salivary flow rate will be collected by sialometry, and recorded in the CRF immediately after collection. The saliva will be saved and stored in a −80 °C freezer until use. All saliva samples stored in the freezer will be recorded and documented in a freezer log. Patient-reported outcomes will be assessed using the two questionnaires, the EORTC QLQ-H&N35, with a focus on domains for dry mouth (HNDR), domains for sticky saliva (HNSS), and domains for swallowing (HNSW), and the XQ. The patients can answer the questionnaires on-site or at home via unique links sent directly to the database. All adverse events are monitored during the trial. Blood samples will be collected at all the visits to monitor the development of HLA antibodies. The results obtained from the blood samples are directly entered into the patient’s medical record by the laboratory.

Any data insertions or corrections in the CRF will automatically be noted in a data log audit trail. The log audit identifies and records all activities carried out by each individual user, including the data accessed or modified, as well as the patients’ record IDs. A data management plan for the will be completed.

### Data management

All data will be documented on-site in a secure web database, REDCap. Data accuracy will be checked by the principal investigator and the data monitor. The REDCap system will raise queries if discrepancies or errors are spotted.

### Statistical methods

The analysis will be performed on the intention-to-treat population (ITT) and a statistical analysis plan will be completed before the end of the study. The primary endpoint is change in unstimulated whole saliva flow rate. The change in saliva flow rate from baseline to 4-month follow-up visit will be presented as change in mL/min and percentage change. The secondary endpoint of stimulated whole salivary flow rate will also be presented as change in mL/min and percentage change. Patient-reported outcome measurements will be evaluated as the changes from baseline to the 4-month follow-up visit and will be presented as a summary score ranging from 0 to 100. An ANCOVA model will be used to analyse continuous outcome measures (change from baseline). The baseline value will be included as a continuous covariate and the randomised treatment group will be included as a categorical variable. Data will be analysed after all patients have completed their 4-month follow-up time, and after the 12-month follow-up time.

Upon completion of the 4-month follow-up visit for all patients, the data will be unblinded, and an analysis of the 4-month follow-up data will be conducted. Subsequently, the long-term follow-up analysis will take place once all patients have completed their 12-month follow-up.

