### Outcomes

The primary endpoint is to evaluate the impact of ASC injections on unstimulated salivary gland function compared to placebo in patients with previous head and neck cancer. The change is evaluated from baseline to month four.

Secondary endpoints are as follows:

To compare the effect of ASC injection, relative to placebo, from baseline to month four on all of the following outcome measurements:Change in stimulated salivary gland function.Change in the patient-reported outcome of xerostomia: The European Organisation for Research and Treatment of Cancer Quality of Life Questionnaire, Head and Neck-35 (EORTC QLQ-H&N35):Domains for dry mouth (HNDR)Domains for sticky saliva (HNSS)Domains for swallowing (HNSW)Change in the patient-reported outcome of xerostomia: Xerostomia Questionnaire (XQ).Change in the composition of salivaSafety evaluated by the development of treatment-related adverse events, serious adverse reactions, or deathImmune response to allogeneic ASC measured by the development of de novo HLA

Tertiary outcomes are as follows:

The change in unstimulated whole salivary flow rate, stimulated whole salivary flow rate, patient-reported outcome of xerostomia evaluated by two questionnaires (EORTC QLQ-H&N35 and XQ), composition of saliva, safety, and immune response in patients receiving ASC injection compared to placebo is further evaluated at 12 months.

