Patients are followed up after 4 month (+/− 14 days) and after 12 months (+/− 4 weeks). At the follow-up visits, patients will undergo saliva flow measurements, have analyses of saliva composition, have blood samples taken (for HLA antibodies), fill out QoL questionnaires, and have an ultrasound exam of the submandibular salivary glands. Lastly, all adverse events are monitored throughout the study period, from the time of treatment until the last day of follow-up (Fig. 1). When all study participants have completed the 4-month follow-up data will be unblinded. All data will be documented on-site in a secure web database, REDCap (Fig. 2).

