## Trial status

Recruitment of participants began in February 2021 and was finished by February 2023. The last patient/last visit is anticipated to be in February 2024. The trial is currently working to protocol version 2.10 dated 25 January 2023. It was not possible to submit the protocol earlier due to adjustments in the method, and the newest protocol version being finalised by 25 January 2023.

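### The SAP deadline is tied to the end of the study rather than to the 4-month unblinding, so the choices still open in the primary analysis could be settled after results by arm are known

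*Protocol article*

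**What the plan says.** All references are to the protocol article.

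- **SAP deadline.** Statistical methods: "a statistical analysis plan will be completed before the end of the study". No sentence ties the SAP to a database lock or to unblinding.
- **Primary time point.** Outcomes: "The change is evaluated from baseline to month four".
- **Unblinding.** Participant timeline: "When all study participants have completed the 4-month follow-up data will be unblinded". Statistical methods repeats the trigger and puts unblinding ahead of the analysis: "the data will be unblinded, and an analysis of the 4-month follow-up data will be conducted".
- **Follow-up after that.** Statistical methods: "Subsequently, the long-term follow-up analysis will take place once all patients have completed their 12-month follow-up". Trial status: "The last patient/last visit is anticipated to be in February 2024".
- **Masking.** Blinding: "Data analysts will further use a dataset where the groups are masked". Allocation restricts the randomisation table to one person until the trial ends and has the code envelopes monitored so that they stay closed until the study ends.
- **Already specified.** Statistical methods names the ITT population and an ANCOVA on change from baseline, with the baseline value as a continuous covariate and treatment group as a categorical variable. The primary outcome is to be presented both in mL/min and as a percentage; the section does not say which is tested.

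**The concern.** An SAP protects the primary comparison only if it is closed before anyone who shapes it can see outcomes by arm. Here the deadline hangs on a later event than the unblinding. A team that follows the text exactly could complete the SAP with the month-4 results by arm in hand.

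Leaving detail to an SAP is normal, and the missing detail is not the complaint. The complaint is the date the article sets for the document that will hold that detail. At stake is whether the 0.05 level given under Sample size applies to one comparison chosen in advance or to the more favourable of two or more.

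The two scales are not interchangeable. Sample size itself pairs an increase of about 33% with a move from 0.125 to 0.155 mL/min, which is 0.030/0.125 = 24%.

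**Working it through.** **1. Timeline.** Inputs: recruitment finished by February 2023 and last visit February 2024 (Trial status); visits at 4 months ± 14 days and 12 months ± 4 weeks (Participant timeline).

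- Check of the stated date: February 2023 + 12 months = February 2024, which agrees with Trial status.
- Last 4-month visit: February 2024 − (12 − 4) months = about June 2023.
- Gap from unblinding to last visit: 12 − 4 = 8 months, or 8 × 30.44 = 243.5 days.
- For a single patient, the visit windows can move this by 14 + 28 = 42 days: 201.5 to 285.5 days, or about 6.6 to 9.4 months.

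If the SAP had to precede the 4-month unblinding, the window would be 0.

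**2. Which end of study is meant.** The term is not defined. Harms speaks of a 12-month study period, Participant timeline follows adverse events to the last day of follow-up, and Trial status puts the last visit in February 2024. Against these, the pregnancy exclusion under Eligibility criteria refers to a study period of 4 months. The balance favours month 12.

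**3. What is still open.** Population, time point, model and covariate are fixed. The tested scale is not named. Sample size expects about 20% dropout; the article does not say how those patients' data are handled, which is properly left to the SAP but is then subject to the SAP's date.

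**4. Illustration of size.** The documents give no SD, so every distributional input is assumed: no treatment effect, 60 per arm, baseline uniform on 0.05-0.25 mL/min (the eligibility range), normal change with the SD shown, month-4 flow not below zero, and data missing at random in the proportion shown. The middle SD is the one implied by 50 per arm for a difference of 0.03 at two-sided 0.05 and 80% power: 0.03 / [(1.960 + 0.842) × √(2/50)] = 0.0535. Each row is 6,000 simulated trials. Entries are the percentage with p < 0.05.

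| SD of change | Missing | ANCOVA on mL/min, fixed | Better of mL/min and % | Also choosing completers or no-change imputation |
|---|---|---|---|---|
| 0.04 | 0% | 4.77 | 6.60 | 6.60 |
| 0.04 | 10% | 4.82 | 7.05 | 7.30 |
| 0.04 | 20% | 4.75 | 6.35 | 6.73 |
| 0.0535 | 0% | 5.22 | 7.20 | 7.20 |
| 0.0535 | 10% | 4.88 | 6.95 | 7.27 |
| 0.0535 | 20% | 4.73 | 6.87 | 7.13 |
| 0.07 | 0% | 4.88 | 6.95 | 6.95 |
| 0.07 | 10% | 4.85 | 6.78 | 7.05 |
| 0.07 | 20% | 5.13 | 6.65 | 7.03 |

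The Monte Carlo standard error near 7% is √(0.07 × 0.93/6000) = 0.33 percentage points. One fixed ANCOVA holds about 5%. Free choice of scale gives about 6.4-7.2%, and adding the missing-data choice gives about 6.6-7.3%.

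**The case against.** **Most of the analysis is already fixed.** This stands. A reader might infer that the whole primary analysis could be settled after the fact, but population, time point, ANCOVA and covariate are in the article. A switch to a t-test, for example, would depart from the stated method, so no such option is counted above.

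**The scale may be less open than it looks.** Presenting both scales is reporting language, and an ANCOVA on change with the baseline value as covariate fits mL/min most naturally. That is a fair reading, but the article does not say so.

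**Missing-data rules belong in the SAP or the full protocol.** Correct, and their absence here is not criticised. An unseen document may already settle them. The point is that the stated deadline does not require that before unblinding.

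**The study's end may mean month 4.** The 4-month study period in the eligibility criteria, and envelopes that stay closed to the study's end although data are unblinded at month 4, give this some support. On that reading the SAP would come before or close to unblinding. The 12-month statements weigh more heavily, and on either reading the sentence needs a defined event.

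**Analysts are masked.** A reader might infer that unblinding before analysis contradicts the Blinding section. That is not established: the unblinding sentences do not say who is unblinded, and analysts could work on masked labels. It is a tension to be reconciled. Masked labels in the dataset also set no date for the SAP.

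**Conclusion.** The point holds in bounded form. As written, the plan permits the SAP to be finalised up to about 8 months (6.6 to 9.4 with visit windows) after the month-4 primary data are unblinded, provided the study ends at the last 12-month visit. The exposure lies mainly in the choice of scale and in whatever handling of dropout is left to the SAP. Its size is modest: roughly 6.4-7.2% in place of 5% for a free choice of scale, on assumed distributions that the documents neither support nor exclude.

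A reader might go further and infer that the SAP was written late. The article was published on 1 September 2023, after the implied unblinding in about June 2023, and still places the SAP in the future. But submission precedes publication, and the SAP is not shown. Nothing shows that it was late; the finding concerns the sequence the text allows.

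**What to change.** - In Statistical methods, state that the SAP is finalised, signed and dated before the 4-month database lock and before any unblinding, and that it names the one scale (mL/min or percentage change) tested in the primary ANCOVA.
- Run that ANCOVA on masked groups, as the Blinding section already provides, and break the code afterwards.
- Define the end of the study, and reconcile Participant timeline, Allocation, Blinding and Statistical methods on who is unblinded and when.
- If the code is already broken, which the dates make likely, the first two steps can no longer protect the analysis unless they were in fact followed. In that case report the SAP date relative to unblinding and label any choice fixed later as post hoc.

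The cost is an earlier SAP date and a few sentences of text. It needs no extra patients and no new data.

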### Eligibility criteria

The inclusion criteria are as follows:Are between 18 and 75 yearsPreviously have been treated with radiotherapy +/− chemotherapy for a head and neck cancerHave a 2 years follow-up without recurrenceHave a clinically reduced unstimulated whole saliva flow rate between 0.05 and 0.25 ml/min evaluated by sialometry

The exclusion criteria are as follows:Have had any cancer in the previous 4 years (not including the head and neck cancer and basocellular carcinomas)Receive xerogenic medicationsHave a penicillin or streptomycin allergyHave any other diseases of the salivary glands, e.g. Sjogren’s syndrome or sialolithiasisPreviously had submandibular gland surgeryPreviously had treatment with any type of stem cells in the saliva glandsAre pregnant or had a planned pregnancy within the 4 months study periodAre breastfeedingHave been smoking within the previous 6 monthsHave a current alcohol abuse (consumption must not exceed 7 units/week for women and 14 units/week for men (Danish National board health alcohol guidelines [17])Have any other disease/condition judged by the investigator to be grounds for exclusion

The criteria for withdrawal from the study are as follows:PregnancyInfection of the transplanted siteWithdrawal of consent from the participant^1^Cigarette smokingCancer (recurrence or new primary cancer, excluding basocellular carcinomas)

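### The primary ANCOVA is valid but leaves unused the baseline stimulated flow that the trial already measures; pre-specifying it as a second covariate may gain some precision at almost no cost.

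*Protocol article*

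**What the plan says.** All references are to the protocol article.

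- **Statistical methods, endpoint.** "The primary endpoint is change in unstimulated whole saliva flow rate", assessed from baseline to month 4.
- **Statistical methods, model.** Continuous outcomes are analysed as change from baseline by ANCOVA: "The baseline value will be included as a continuous covariate and the randomised treatment group will be included as a categorical variable". No other covariate is named and none is ruled out. The section adds that "a statistical analysis plan will be completed before the end of the study".
- **Data collection methods.** "Unstimulated whole salivary flow rate and stimulated whole salivary flow rate will be collected by sialometry", at baseline and at both follow-up visits.
- **Outcomes.** Change in stimulated salivary function from baseline to month 4 is a secondary endpoint, so a baseline stimulated value must exist.
- **Eligibility criteria.** Entry requires a "clinically reduced unstimulated whole saliva flow rate between 0.05 and 0.25 ml/min evaluated by sialometry".
- **Sample size.** 50 per group for 80% power at an alpha of 0.05, raised to 120 in total for about 20% dropout. No standard deviation and no correlation is given.
- **Participant timeline and Statistical methods.** Data are unblinded once all patients have completed month 4.

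**The concern.** Stimulated flow is a second reading of residual gland function, taken in the same patients before treatment. If it predicts month-4 unstimulated flow beyond what baseline unstimulated flow predicts, leaving it out makes the residual variance of the primary comparison larger than it needs to be.

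The trial was planned at 80% power with little slack: 120 less 20% leaves 96 patients, slightly under the planned 100. Recruitment had finished by February 2023 (Trial status), so the sample can no longer grow. Covariate adjustment is one of the few remaining ways to tighten the interval for the cell effect.

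In a linear model, a pre-specified baseline covariate leaves the target (the difference in mean change) as it is and does not compromise the randomised comparison.

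**Working it through.** **Inputs from the protocol article.** Sample size: 50 per group, power 0.80, alpha 0.05, expected change from 0.125 to 0.155 mL/min, so a difference of 0.030. Allocation: 1:1.

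**Assumptions.** The test is two-sided (sidedness is not stated). The 80% refers to the stated single-covariate model. *r* is the partial correlation of baseline stimulated flow with the outcome, given baseline unstimulated flow and treatment. Because baseline unstimulated flow is in the model, *r* is the same whether the outcome is change or the month-4 value.

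**Step 1: the plan's own figure.** Without a standard deviation, 50 per group can be inverted but not reproduced. The standardised difference giving 80% power is (1.960 + 0.842)/√(50/2) = 2.802/5 = 0.560. The implied residual SD is 0.030/0.560 = 0.0535 mL/min.

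**Step 2: effect of a second covariate.** Residual SD becomes 0.0535 × √(1 − r²). Power is approximately Φ(2.802/√(1 − r²) − 1.960). The reduction in standard error is 1 − √(1 − r²).

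| r | Residual SD (mL/min) | SE reduction | Power, 50 per group | Power, 48 per group |
|---|---|---|---|---|
| 0 | 0.0535 | 0% | 80.0% | 78.4% |
| 0.1 | 0.0533 | 0.5% | 80.4% | 78.8% |
| 0.2 | 0.0525 | 2.0% | 81.6% | 80.0% |
| 0.3 | 0.0511 | 4.6% | 83.6% | 82.1% |
| 0.4 | 0.0491 | 8.3% | 86.4% | 85.0% |

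The last column uses 120 × 0.8 = 96 evaluable patients, that is 48 per group, with the same SD.

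**Step 3: cost of the extra term.** Estimating one more coefficient inflates the variance by roughly 1/(N − 4). With N = 100, break-even is at about r = √(1/96) = 0.10. Below that there is nothing to gain, and the loss is negligible.

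**Step 4: what values of r are plausible.** The documents do not say. As a purely illustrative assumption, if baseline unstimulated, baseline stimulated and month-4 unstimulated flow all correlate equally at ρ, then r = ρ/(1 + ρ). This gives 0.3/1.3 = 0.23, 0.5/1.5 = 0.33 and 0.7/1.7 = 0.41. If the two baseline flows overlap more closely with each other than with the outcome, r is smaller.

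**The case against.** **The model contains no mistake.** ANCOVA on the outcome's own baseline is standard and unbiased under randomisation. A second prognostic covariate is an efficiency choice. This stands, and it limits the point to a suggestion.

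**The analysis plan may already name further covariates.** It is not shown, and the article excludes none. This also stands. The article does state a covariate set, however, and it asks for the analysis plan only before the end of the study, with the last visit expected in February 2024. Unblinding comes earlier. A covariate added between those two dates would meet the stated deadline but would not be credible as primary.

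**The 80% anchor is uncertain.** The Sample size section gives no SD and does not mention ANCOVA. If the SD behind it was unadjusted, the stated model may already exceed 80%, and the gains in power points would differ. The proportional reductions in standard error would not.

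**Two stronger readings that the documents do not support.**

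- A reader might infer that the 0.05–0.25 mL/min entry window weakens the baseline covariate and so costs precision. It does not follow. Precision depends on residual variance, not on the correlation. In an illustration with log-normal flows (median 0.15, log-SD 0.6, log-scale correlation 0.7; all assumed), restricting to the window lowers the correlation from 0.66 to 0.50. The residual SD of the month-4 value also falls, from 0.089 to 0.071 mL/min. The window gives no reason to add a covariate.
- A reader might also infer that stimulated flow escapes the entry restriction. It has no direct limit, but if it correlates with unstimulated flow, selection on the latter narrows it indirectly.

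**It may be too late.** A last 12-month visit in February 2024 points to a last 4-month visit around mid-2023, before the article's publication in September 2023. This is an inference from dates; the documents do not state when unblinding took place.

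**Conclusion.** The point holds as a low-severity efficiency improvement. The stated primary model is sound; it does not use a baseline measurement that the trial collects anyway.

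The gain ranges from nothing (r up to about 0.1), through roughly 2 to 4 power points (r of 0.2 to 0.3), to about 6 points (r of 0.4). These figures rest on a two-sided test, 50 per group, 80% power for the stated model, and an assumed partial correlation. It would overstate the case to say that precision is certainly being lost: whether it is, and how much, turns on a correlation that the documents do not report.

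**What to change.** **If the 4-month data are still blinded:** state in the Statistical methods section or the analysis plan that the primary ANCOVA of change in unstimulated flow at month 4 includes treatment, baseline unstimulated flow and baseline stimulated flow, both flows as continuous covariates. Report the single-covariate model as a sensitivity analysis.

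**If unblinding has already happened:** keep the stated single-covariate model as primary and report the two-covariate model as a labelled sensitivity analysis.

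**Cost:** one sentence, one degree of freedom and no new data. If the partial correlation is near zero there is no gain.
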